## SPIRIT diagram of enrolment, interventions and assessments

### Intervention

rTMS treatment will be performed first, and Tui Na treatment will be performed immediately after rTMS treatment. All patients will receive the treatment plan for twenty sessions over 4 weeks with Tui Na for 30 min and rTMS for 10 minevery session (Figure 2).

**Figure 2 F2:**
[figure not shown]
rTMS synergize with Tui Na treatment.

#### rTMS

rTMS intervention will be performed using a transcranial magnetic stimulator (MagTD; Wuhan Yiruide Medical Equipment New Technology Co., Ltd., Wuhan, China) and a figure of eight coil (YRD, maximum magnetic field intensity = 2T, diameter = 9 cm, Wuhan Yiruide Medical Equipment New Technology Co., Ltd.). First, the resting motion threshold (RMT) of rTMS will be determined. The surface recording electrode will be placed at the abdomen of the abductor pollicis brevis muscle on the affected side (if MEP is not detected, the unaffected side will be used) of the UL, the reference electrode will be placed at the tendon, and the ground wire will be connected to the wrist. Adjust the central position of the magnetic stimulation coil to the best position of motor evoked potential (MEP) of abductor pollicis brevis, and gradually reduce the stimulation. In the resting state, at least 5 of the ten stimuli with a minimum magnetic stimulation intensity of >50 μV MEP amplitude will be considered RMT on the side of the cerebral cortex. During the treatment, the patient will be in the supine position, and the motor area of the ipsilesional side of the brain (M1) will be used as the stimulation target. The “8” coil is tangent to the surface of the skull, the midpoint will be aimed at the stimulation target, the stimulation intensity is 100% RMT, the stimulation frequency is 10 Hz, each sequence is 20 pulses, the sequence interval is 8s, with a total of 1200 pulses in 10 min. The patients will be treated 5 times a week for 4 weeks.

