## Abstract

Upper limb motor dysfunction after stroke is a serious threat to the living quality of patients and their families. Recovery of upper limb motor function after stroke largely relies on the activation and remodeling of neural circuits. rTMS (repetitive transcranial magnetic stimulation) has been proved to promote the reconstruction of neural synapses and neural circuits. However, there are still a large number of patients who cannot fully recover and leave behind varying degrees of dysfunction. Considering the systemic pathology after stroke, in addition to focal brain injury, stroke can also cause extensive dysfunction of peripheral organs. The rehabilitation strategy for stroke should combine the treatment of primary brain lesions with the intervention of secondary systemic damage. The aim of this trial is to verify the efficacy of rTMS synergize with Tui Na (Chinese Massage) on upper limb motor function after ischemic stroke, and to explore the mechanism of activation and remodeling of sensorimotor neural circuits with functional near-infrared spectroscopy. Ninety patients will be randomly assigned to either rTMS + Tui Na + conventional rehabilitation group (the experimental group) or rTMS + conventional rehabilitation group (the control group) in 1:1 ratio. Intervention is conducted five sessions a week, with a total of twenty sessions. The primary outcome is Fugl-Meyer Assessment, and the secondary outcomes include Muscle Strength, Modified Ashworth Assessment, Modified Barthel Index Assessment, motor evoked potentials and functional near-infrared spectroscopy. There are four time points for the evaluation, including baseline, 2 weeks and 4 weeks after the start of treatment, and 4 weeks after the end of treatment. This study is a randomized controlled trial. This study was approved by Institutional Ethics Committee of Shanghai Third Rehabilitation Hospital Affiliated to Shanghai University of Traditional Chinese Medicine (approval No. SH3RH-2021-EC-012) on December, 16th, 2021. The protocol was registered with Chinese Clinical Trial Registry (ChiCTR2200056266), on February 3th, 2022. Patient recruitment was initiated on February 10th, 2022, and the study will be continued until December 2023.

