### Outcome measures

The assessment will be conducted on four time points, including at baseline, 2 weeks and 4 weeks after the beginning of the treatment, and 4 weeks after the end of the treatment (Table 1). All assessments will be performed by therapists who do not know the specific group.

**Table 1 T1:** SPIRIT figure.

	**Screening**	**Baseline**	**Intervention**			**Follow weeks**
Time Point	**-t** _ **2** _	**-t** _ **1** _	**0**	**w2**	**w4**	**4w**
Enrollment						
Informed consent	**√**					
Demographic information	**√**					
Medical history	**√**					
MMSE	**√**					
Eligibility assessment	**√**					
Random allocation		**√**				
Interventions						
Tui Na+TMS group						
Cnventional group						
Assessments						
Fugl-Meyer-UE		**√**		**√**	**√**	**√**
MS		**√**		**√**	**√**	**√**
MAS		**√**		**√**	**√**	**√**
MBI		**√**		**√**	**√**	**√**
MEP		**√**		**√**	**√**	**√**
fNIRS		**√**		**√**	**√**	**√**
Adverse event			**√**	**√**	**√**	**√**

Description of the protocol. -t2, first contact with participants; -t1, baseline evaluation;0, starting day of the treatment; w2, 2weeks after the start of treatment;w4, 4 weeks after the start of treatment and post evaluation;4w, 4 weeks after the end of treatment; MMSE, Mini-Mental State Examination; Fugl-Meyer-UE, Fugl-Meyer Upper Extremity Scale; MS, Muscle Strength; MAS, Modified Ashworth, MBI, Modified Barthel Index; MEP, Motor evoked potentials; fNIRS, functional near-infrared spectroscopy; The orange line represents the treatment time in the figure, with a total of 4 weeks of treatment.

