#### Motor evoked potentials

MEP is the muscle motor potential recorded by stimulating the motor cortex in the target muscle, and to examine the overall synchronization and integrity of the motor nerve transmission from the cortex to the muscle and the conduction pathway. TMS results in sequential activation of upper motor neurons, which in turn leads to spinal cord motor neuron activation, and is recorded by the surface Electromyography in the target muscle (32). In this research, at least 5 out of 10 monopulse stimuli will be given to the cortical representative region (M1) of the contralateral abductor pollicis brevis to induce MEP with an amplitude >50 μV as the motor threshold. The resting motor threshold (RMT) will be analyzed.

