#### Comparability analysis

According to the analysis of the basic situation of the two groups before treatment, the sex of the patient will be divided into two variables, and the chi-square test of two independent sample rates will be used. W-test and F-test will be used to determine that the continuous variables such as Fugl-Meyer-UE, MS, MBI and MEP and fNIRS measurements (Lateral Index, RSFC values, zfALFF values) in the baseline is in accordance with normal distribution and homogeneity of variance, and two independent sample *t*-tests will be used for comparison. If these data do not conform to normal distribution or homogeneity of variance, Wilcoxon rank sum test will be used to compare the measurement data. If the comparison of the variables in the baseline between the two groups is statistically significant and professional, the variable will be analyzed as a covariable multiple efficacy index.

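### RMT is the only MEP variable to be analysed, but it has no value in patients without an affected-side MEP, so the change analysis omits them and cannot count a regained MEP

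*Protocol article*

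**What the plan says.** The Abstract names the later secondary outcomes as "Modified Barthel Index Assessment, motor evoked potentials and functional near-infrared spectroscopy". Under Motor evoked potentials, a single variable is chosen for analysis: "The resting motor threshold (RMT) will be analyzed". It is defined by at least 5 of 10 single pulses to the M1 representation "of the contralateral abductor pollicis brevis to induce MEP with an amplitude >50 μV as the motor threshold". The word contralateral there is relative to the stimulated cortex, so it does not say whether the affected or the unaffected side is meant. Response presence, amplitude and latency are not named for analysis.

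Under rTMS, the recording electrode goes on the affected side, with the exception "if MEP is not detected, the unaffected side will be used". The threshold found there sets treatment: "the stimulation intensity is 100% RMT".

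Inclusion criteria select on imaging diagnosis, time since stroke, Fugl-Meyer score, age and MMSE. None requires an MEP. Outcome measures sets the schedule ("The assessment will be conducted on four time points, including at baseline, 2 weeks and 4 weeks after the beginning of the treatment", plus a follow-up visit), and Table 1 ticks MEP at all four visits.

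Comparability analysis groups MEP with "the continuous variables such as Fugl-Meyer-UE, MS, MBI and MEP and fNIRS measurements". Efficacy analysis compares the arms by t-test, or by rank-sum test if normality or equal variance fails. Data set population determination fills missing data by LOCF.

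**The concern.** The variable chosen to represent MEP exists only when an MEP can be evoked. The protocol admits patients in whom it cannot be evoked on the affected side, and it expects to meet them. For these patients the plan offers a continuous-variable comparison and a general missing-data rule, and neither yields a usable value.

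The section says that MEP is measured to examine the integrity of conduction from cortex to muscle. A change from no response to a response bears directly on that purpose. An analysis of RMT alone, treated as a continuous measure, cannot register it. The RMT result would then describe only patients who already had a response at baseline. If post-treatment values are compared instead, it would describe a group whose membership may be shaped by treatment.

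**Working it through.** The plan states no figure for RMT or for the share of patients without an MEP, so there is nothing to reproduce. The check applies each stated rule to one patient and then counts patients under labelled assumptions.

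**One patient: no affected-side MEP at baseline, MEP present at week 4**

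1. Baseline RMT on the affected side: the 5-of-10 criterion cannot be met, so there is no value.
2. LOCF: baseline is the first visit, so no earlier observation exists to carry forward.
3. Change from baseline: week 4 value minus an undefined value cannot be computed.
4. Rank-sum fallback: it is triggered by non-normality or unequal variance. It ranks observed values and says nothing about where an undefined value belongs.
5. Result: the patient is absent from the change analysis and the recovery is not counted.
6. If arms are compared on week 4 values instead, this patient enters. An otherwise identical patient who did not regain an MEP stays out. Entry then depends on a post-randomisation event.

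**How many patients**

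Input from the documents: 45 per arm (Sample size calculation). Assumed input: share q without an affected-side MEP at baseline, 20% to 50%. Dropout is ignored.

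- Without a baseline RMT per arm = q × 45: 0.20 × 45 = 9; 0.50 × 45 = 22.5, about 23.
- With a baseline RMT per arm = (1 − q) × 45: 0.80 × 45 = 36; 0.50 × 45 = 22.5.
- Sample size needed to restore the same number analysed, as a ratio = 1/(1 − q): 1/0.80 = 1.25; 1/0.50 = 2.0.

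**Post-treatment comparison, illustration only**

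Assume further that 40% of these patients regain an MEP in one arm and 20% in the other.

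- q = 20%: 9 × 0.40 = 3.6 against 9 × 0.20 = 1.8 new entrants, so 39.6 against 37.8 analysed.
- q = 50%: 22.5 × 0.40 = 9 against 22.5 × 0.20 = 4.5 new entrants, so 31.5 against 27 analysed.

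The arms would then differ in who is analysed because of the response itself. The documents support neither regain rate; the figures show only the mechanism.

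**The case against.** **The side switch is a dosing rule.** A reader might infer that the plan substitutes the unaffected hemisphere in the outcome data and so scores recovery as worsening. The documents do not support that as a stated procedure. The switch stands in the rTMS section, where RMT sets stimulation intensity. The Motor evoked potentials section has its own definition and neither adopts nor excludes the switch. If it were carried into the outcome data, baseline would come from one hemisphere and week 4 from the other. With an assumed unaffected-side RMT of 45 to 55 and a regained affected-side RMT of 60 to 80 (% of stimulator output), the change would lie between 60 − 55 = +5 and 80 − 45 = +35 points, a rise that reads as deterioration. That is a possible reading with assumed values. This objection stands.

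**Coding of unobtainable values belongs in the SAP.** This stands in part. A coding convention may well sit in a document not shown. But the protocol itself selects RMT as the sole MEP variable, classes MEP as continuous and expects patients for whom that variable has no value. The choice of variable is already fixed here.

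**Other readings are open.** Both hemispheres could be measured, or an absent MEP given a ceiling value, but the article states neither. Using the unaffected side throughout would give these patients values, but would not show the affected side's recovery.

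**Omission is not bias.** Correct for the change analysis: baseline MEP status precedes treatment, so leaving these patients out costs precision and coverage without favouring an arm. It does not hold for a comparison of post-treatment values.

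**Conclusion.** The concern holds in a limited form. The sole analysed MEP variable is undefined in a subgroup that the protocol admits and expects, and none of its stated rules gives that subgroup a usable value. A change analysis loses these patients and misses a regained MEP; a post-treatment comparison could let treatment determine who is analysed.

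The size is unknown. The count of 9 to 23 of 45 per arm rests wholly on the assumed 20% to 50% share, and only the 45 comes from the documents. No effect on a test result can be stated, because no RMT mean or standard deviation is given. One secondary outcome is affected; the Fugl-Meyer analysis and the sample size are not.

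**What to change.** Amend Motor evoked potentials and Efficacy analysis, for the outcome only and with no implication for how stimulation is set:

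- Analyse ipsilesional RMT at every visit, and never substitute the other hemisphere in the outcome data.
- Rank an absent MEP as worst, above maximum stimulator output, and compare arms by ranks.
- Report MEP presence or absence by arm and visit.

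Cost: a few lines of text. MEP is already scheduled at all four visits, but the article does not say that an absent response is recorded as such, so the case report form may need one field and an affected-side attempt at each visit. The drawbacks are ties among all patients without an MEP, and a rank comparison in place of a mean RMT difference. The mean difference among patients with an MEP at baseline can still be reported as a description.

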#### Tui Na

##### Selection-of-acupoints-and-locations

Focus on the acupoints of LI4 (Large Intestine 4), PC8 (Peri Cardium 8), SJ5 (SanJiao), PC6 (Peri Cardium 6), LI10 (Large Intestine 10), LI11 (Large Intestine 11), LU5 (Lung 5), LI14 (Large Intestine 14), LI15 (Large Intestine 15), ST12 (Stomach meridian of foot Yangming 12) for the affected UL. Focus on the acupoints of DU14 (Governor meridian 14), DU4 (Governor meridian 4), GB21 (Gall BLadder 21), BL11 (Bladder 11), BL13 (Bladder 13), BL15 (Bladder 15), BL18 (Bladder 18), BL19 (Bladder 19), BL20 (Bladder 20), BL21 (Bladder 21), BL23 (Bladder 23) for the spine. Acupoints are rich in receptors, so select these acupoints of the affected UL to achieve a comprehensive stimulation of the affected UL. The acupoints around the spine correspond to the viscera of the whole body through the spinal nerve and sympathetic nerve. Stimulating these acupoints can regulate the organs and functions of the whole body.

##### Selection-of-manipulations-and-operating-rules

Kneading, pressing, one-finger meditation and active joint manipulations will be selected. The standard manipulation requires the basic technical requirements of “lasting, powerful, uniform, soft and penetration.” “Lasting” means that the manipulation can be operated continuously for a certain period without interruption to maintain the consistency of movement and strength and to ensure that the amount of stimulation to the body accumulates to a certain extent. “Powerful” means that the manipulation must have a certain strength and reach a certain level. This kind of power is not brute force or violence but a skillful force that is used according to the different people and locations of treatment. “Uniform” means that the manipulation's strength, speed and operating range should be homogeneous, rather than sometimes light and sometimes heavy, sometimes fast and sometimes slow, and sometimes large and sometimes small. “Soft” refers to gentle and rhythmic movements, not stiff, rough, or brute force. “Penetration” means that the stimulation of the manipulation can reach the deep subcutaneous layer and viscera tissue. The above aspects are closely related and complement each other. The continuous use of manipulations can gradually reduce the muscle tension of patients so that the strength of manipulation can gradually infiltrate into the deep tissue. Uniform and coordinated movements can soften the manipulations. The combination of strength and skill makes the manipulation both powerful and soft.

##### Procedure-of-treatment

The affected UL: the patients will be PLACED in a sitting position, and the therapist will focus on the acupoints from the hand to the shoulder to carry out kneading, pressing, one-finger meditation, and active joint manipulations. The appropriate force will be used to make the patient feel sore and distended, and the treatment time is about 15 min.

Spine: the patients will be placed in a prone position, and the therapist will focus on the acupoints from neck to waist to carry out kneading and pressing manipulations. Appropriate force will be used to make the patient feel sore and distended, and the treatment time is about 15 min.

##### Matters-needing-attention-in-treatment

Treatments should be performed in a quiet room. The temperature and humidity should be appropriate. The therapist's hands should be kept clean and warm. Nails should be trimmed frequently so as not to cause discomfort to the patient or even damage the patient's skin. Fully communicate with patients to eliminate their nervousness. Closely observe the reaction of patients to timely adjust the amount of stimulation, and beware of adverse responses or accidents. In the event of an accident, the treatment should be stopped immediately.

#### Conventional rehabilitation

All the patients will receive conventional rehabilitation treatment during the study period, including physical therapy, occupational therapy and drug therapy etc. The patients cannot change the conventional rehabilitation during the study period.

### fNIRS data acquisition

fNIRS equipment (Danyang Huicuang Medical equipment Co., Ltd., Jiangsu, China) will be used to record the hemodynamic data of patients before and after rehabilitation treatment. A total of 21 NIRS optrodes (11 light sources and 10 detectors, with wavelength of 730 and 850 nm, and sampling rate of 19 Hz) forming 32 observation channels. The optrodes will be fixed on the patient's head with a holder, covering the bilateral frontal and parietal regions. Resting-state session and task session will be included in fNIRS evaluation. During the resting-state evaluation, patients will be asked to sit and relax for 8 min, and the resting data will be collected. The task session involved repetitive movements of flexion and extension of the hemiplegic fingers at frequency of 1 Hz with verbal cues, using a block design [six cycles: rest (10 sec); hand movements (15 sec); rest (20 sec)]. A three-dimensional digitizer (Patriot, America) will be used to collect the 3D coordinate information of the optrodes and channels to ensure the accuracy of the observed brain area and to be consistent in multiple measurements. According to the Brodmann area (BA) and anatomical locations of cortex, the observation channels will be divided into six ROIs (regions of interest): ipsilesional premotor cortex, PMC_ipsi; contralesional premotor cortex, PMC_contra; ipsilesional primary sensorimotor cortex, SM1_ipsi; contralesional primary sensorimotor cortex, SM1_contra; supplementary motor area, SMA; Somatosensory Association Cortex, SAC (Figure 3).

**Figure 3 F3:**
[figure not shown]
**(A)** The arrangement map of fNIRS channels in the cortex, which is divided into 6 ROIs. **(B)** Light sources (red dot, 11) and detectors (blue dot, 10) forming 32 channels (yellow line). The sensitivity distribution map of photons in the cortex is simulated by Monte Carlo, and the redder the region is, the stronger the sensitivity is.

### fNIRS data analysis

The fNIRS data will be preprocessed and analyzed using NIRS-KIT (19) and NIRS-SPM v.3.2 (20, 21) based on MATLAB 2013b (The MathWorks Inc., Massachusetts). Considering that HbO signal has been widely used in studies of clinical interventions (22), with better sensitivity to task-related hemodynamic changes (23), and found excellent reliability for both task-related activity (24) and resting-state functional connectivity (RSFC) (25) in test-retest studies, we will focus on HbO signal in present protocol study. fNIRS data will be preprocessed with a first order detrend to remove liner trends and Temporal Derivative Distribution Repair (TDDR) algorithm to correct motion artifacts (26).

For task-related assessment, fNIRS data will be further smoothed with the canonical HRF. The General Linear Model (GLM) will be used to detect the hemodynamic activities of the NIRS time-series. The design matrix consisting of a boxcar regressor of motor task will be convolved with a Gaussian HRF to obtain the predictors of the time series of neural activation. Beta-estimates represent the weight of motor task to the variance of the hemodynamic signal of each channel. Cortical activation will then be calculated with a contrast vector of [1–1], and significance will be set at p < 0.05. All activation results will be corrected by multiple comparisons using the Tube formula method in NIRS-SPM. The number of activated channels in the contralateral and ipsilateral hemisphere will be used to calculate the Lateral Index, LI = (contralateral – ipsilateral) / (contralateral + ipsilateral).

For resting-state assessment, data segment of 7-min in the middle of resting-state session will be used to analyze RSFC. After detrend and motion-artifact correction, fNIRS data will be bandpass filtered (0.01 to 0.08 Hz) using a third-order IIR filter. RSFC will be calculated by Pearson's correlation with Fisher-z score conversion, on levels of ROI2ROI, ROI2Whole-brain, and whole brain (channel -wise). Furthermore, the amplitude of low frequency fluctuations (ALFF) will be computed by Fourier transform, and then fractional ALFF be calculated by the ratio of power spectrum of low-frequency (0.01–0.08 Hz) to that of the entire frequency range (27). The fractional ALFF values will be standardized by Fisher-Z conversion as zfALFF, for further statistics. All correlation coefficients will be first analyzed by False Discovery Rate correction (FDR correction) and then analyzed by intra-group and inter-group statistics.

